[58]. This is done at the first treatment occasion. The participant identifies six specific main problems together with the IL, and rate the difficulty and importance of each problem respectively, on 0–7 scales (higher scores mean more difficult/more important). Finally, the identified problems are ranked by the participant in terms of significance. The top three ranked problems are considered in the final composition of treatment components for the participant in the T-group as well as on the functional training of daily activities (see *Functional training of daily activities* below). After the PET interview, the IL and the PL meet to settle the final treatment direction. To this end, the outcome of the PET is considered together with the result of the decision model within predetermined rules (see *Rules for the decision model* below). Also, the prioritization order among treatment components is discussed if the participant has several (>3) in her treatment profile. The degree of impairment in relation to cut-off limits for each component as well as the outcome of the PET are considered if a priority order is set. Participants allocated to the NT-group are also interviewed at the first treatment occasion, but the questions included concern anamnesis and status focused on symptoms. The interview in both treatment groups is concluded by asking the participants what their personal goal with the rehabilitation would be. For the T-group, this goal should be connected to the specific activities listed in PET.

To identify participants that may have a need for optical correction and/or Visual Display Unit eye-glasses the following questions are asked: 1. *Do you wear spectacles, prescribed by a certified optician during the last 2 years, for near distance work?* 2. *Do you regularly perform visually demanding near-work, such as working with a computer or any other visually demanding near-work tasks, which requires a well functioning near vision?* If the answer is “yes” on the latter question, participants also answer 3. *Do you experience strain in or around your eyes at such work tasks?* The following combinations of answers qualify to be assessed by an optician: Participants ≥40 years of age; “No” on question 1 and “Yes” on the second question. Participants <40 years of age; “No” on question 1, “Yes” on question 2 and “Yes” on the third question. Only participants allocated to the T-group are sent to optician on qualification.

### Treatment components

The following treatment components were included (cf. corresponding factors and tests described in Table
2 as indicated by their numbers):

1. Manual therapy including mobilization treatment and training to promote range of motion, derived from the main factor *1. Cervical flexibility.* The three sub-factors shown in Table
2 (1.1, 1.2, 1.3) outline largely the cervical levels and the planes of motion to be treated. However, the specific cervical levels of manual mobilization/ROM-training as well as the target of structure (e.g. joint structures and/or extraarticular tissue like muscles and connective tissues) are decided by the therapist according to manual therapy principles
[59]. Note that participants qualified according to the sub-factor 1.3 receive mobilization/ROM-training in rotation of the upper cervical only if cut-off 1.1.b. is reached.

2. Cranio-cervical flexion (CCF) exercise and strength training neck-shoulder-arm, derived from the main factor *2. Cervical strength*. The sub-factor 2.1 qualifies for specific CCF exercise program
[60,61]. Sub-factor 2.2 entails moderate to high intensity strength training targeting neck-shoulder muscles. The program is inspired by Ylinen and co-workers
[62] and the American College of Sports Medicine Position Stand
[63], the latter regarding principles for movement speed, dose, load and frequency. 2.3 regards strength training for shoulder-arm muscles. The same training principles is used here as in 2.2.

3. EMG-biofeedback training, derived from factor *3. Trapezius myalgia*. The biofeedback treatment program consists of eight standardized exercises with gradual progression of difficulty level followed by training in specific tasks individualized for each participant in the tailored treatment group. For example, the specific task training could include wearing EMG-biofeedback equipment while working at a simulated computer-workstation with a stressful task. In this situation, postural corrections and re-education with the help of biofeedback may take place. The aim is to teach/train the participant to relax the upper trapezius muscles both in resting position and in static and dynamic tasks (to lower the contraction level of the trapezius muscle, obtain muscle relaxation in between contractions and to optimize the muscle strain during the task).

4. Treatment program for cervicogenic headache (factor 4 in Table
2). This is composed of manual therapy for the upper cervical and therapeutic exercise including CCF exercise and low-load endurance training for scapular muscles, mainly the lower trapezius and the serratus anterior, as well as postural correction of scapula in sitting. Thus, the treatment is adapted to current best evidence
[64,65].

5. Neck coordination training / motor control training deriving from factor *5. Sensorimotor control*. There are two sub-factors delineated in Table
2: *5.1. Symptoms and activity limitations* and *5.2. Cervical motor function*. Participants qualifying for 5.1. receive a training program with exercise progressions of difficulty in three levels. The program is based on the work of Kristjansson and Treleaven
[56,57] and consists of two main types of exercises: cervical repositioning/movement control and occulomotor exercises. The latter type consists of smooth pursuit, saccades, gaze stability and eye-head coordination exercises. Training of postural stability is usually an important component for patients with neck-shoulder pain and dizziness/unsteadiness. We have chosen to integrate this component in the other exercises at the third level of difficulty. Training following *5.2. Cervical motor function* focuses on improving the ability to perform fast cervical rotations. This may be done with partly the same exercises as in 5.1., but also in a dark room letting light flashes guide quick head movements in different movement planes and with varying trajectory length. In order to promote motor learning of the exercises including retention and transfer to other tasks and contexts, principles of motor learning theory
[66] is part of the training program. For example, random practice in different contexts is introduced in order to enhance retention and transfer, and both internal (tactile, visual, proprioceptive) and external (verbally or by video) feedback is used to endorse the learning process.

A third treatment component could also be considered in the T-group if PET clearly indicates problems with activities that have close relation to a function/test included in the decision model, and the result of that test was close to cut-off for the specific individual.

If a participant experiences acute problems that negatively influence functions not included in her treatment component profile, the line of action from the therapist is first watchful waiting with adjustment of the participant’s current components during one week. If the problem remains after one week, the therapist is allowed to assess and treat with manual therapy maximally three times to reduce pain
[3,15] irrespective of the participant’s treatment profile.

### Functional training of daily activities

In the latter half of the intervention period, functional training of daily activities is introduced and the treatment component program correspondingly reduced. For the participants of the T-group, each treatment component has predetermined suggestions for functional training exercises as a basis, but the idea is to individualize this part as far as possible. A meeting is held between IL and a person in the project group before commencing the training to discuss ideas for individual-specific functional training that targets the problematic activities pinpointed by the PET. Special concern is taken to organize the training according to principles of motor learning theory in order to enhance retention of the functional training tasks and transfer to new tasks and environments
[66]. Thus, variation of the training/random practice is emphasized
[67] with a gradual progression towards training in different contexts and increasingly more complex movement tasks, and external feedback is used. The functional training for the participants of the NT-group follows a set training program with complex movement exercises called “Muscle Action Quality (MAQ) training”
[68]. The exercises are believed to enhance the general fitness qualities strength, flexibility, balance and movement control. The program is the same for all NT-group participants and includes movement exercises without weights and diagonal press- and pull exercises with weights. Thus, the exercises are not linked to specific daily activities as is the case for the T-group.

### Assessment

The baseline assessment has the following components and purposes: i) laboratory assessment including tests of motor control, strength and activity limitations, used for the treatment decision model as well as treatment outcome measures ii) clinical examination to categorize participants according to specific diagnostic criteria
[26,27,55,69,70] used for the treatment decision model iii) clinical examination to confirm inclusion and exclusion criteria iv) questionnaires used for the treatment decision model and treatment evaluation. During a period of three months before commencing the study, the test leader was trained in performing assessments included in the test protocol. The test leader is blinded with regard to the group allocation of each subject.

### Laboratory assessment, test of functioning

The laboratory assessment described in this section correspond to factor 1 (*Cervical flexibility*), 2 (*Cervical strength*) and 5 (*Sensorimotor control*) in Table
2.

#### Cervical flexibility and Sensorimotor control

Cervical flexibility is measured in tests of active range of motion of the upper and lower cervical spine in flexion-extension and of axial rotations in normal upright posture. The procedures for these tests are identical to the descriptions given in
[44]. Also, range of motion of axial head rotation during maximal forward neck flexion is measured. The test procedure is identical to that of Amiri et al.
[45] except for that the axial rotations are passively imposed by the test leader and only two repetitions to each side (right/left) are performed. Cervical motor control is assessed in a test of maximal speed of cervical axial rotations
[32]. All tests are performed in sitting and are given in the order in which they are described above. Kinematics of head movements relative to the thorax are measured with an electromagnetic tracking system (FASTRAK™, Polhemus Inc, USA)
[45]. Outcome measures for the tests are maximum range of movement (degrees) and peak angular speed of the cervical axial rotations (degrees/second).

#### Cervical strength, cervico-thoracic test

Cervico-thoracic extension and flexion (Figure
2) maximal voluntary contraction (MVC) is performed in sitting with the same procedure as Salo and co-workers
[49]. The strength values are expressed in Newtons.

**Figure 2 F2:**
[figure not shown]
**Cervico-thoracic flexion test.** Sitting measurement of isometric cervico-thoracic flexion strength, maximal voluntary contraction (with permission).

#### Cervical strength, cranio-cervical flexion test

The measurement device used for this test is based on O’Leary et al.
[71], but in conformity with Van Wyke et al.
[72] the test is performed in a standing position (Figure
3). In the starting position the dynamometer resistance arm of the measurement device is placed under the inferior border of the participant’s mandible. The dynamometer axis is aligned to the concha of the ear which corresponds to the axis of rotation for the atlanto-occipital joint over which the cranio-cervical flexor muscle group (the longus capitis and rectus capitis anterior muscles) acts. After getting accustomed to the device, instructions and a practice session in doing an isolated cranio-cervical flexion movement, the participant performs three maximum effort trials. If the last trial exceeds the second last by >5%, then a further trial is carried-out. Thereafter, the test leader explains and visualizes the endurance 50% MVC test with help of a computer screen showing the level of 50% MVC. The participant is asked to press against the resistance arm so that the torque curve reaches the 50%-level and to keep it there as long as possible. If the torque drops below the 50%-level, the test leader immediately instructs the participant to return to the level. The test ends either because of failure to keep the torque at the required level or when 10 accumulated seconds below the 50%-level bar has passed. The outcome of cranio-cervical flexion MVC test is torque (Newtonmeter) and the endurance 50% MVC test is time (seconds).

**Figure 3 F3:**
[figure not shown]
**Cranio-cervical flexion test.** Standing measurements of isometric cranio-cervical flexion strength, maximal voluntary contraction, and endurance 50% of maximal voluntary contraction (with permission).

#### *Cervical strength*, *arm strength in lifting task*

The cervical progressive isoinertial lifting evaluation test (C-PILE) involves lifting weights placed in a box from waist height to shoulder height with progressively increasing loads
[51,73,74].

### Clinical examination

#### Categorizing individuals with neck pain

Neck pain participants are examined by a physiotherapist according to a standardized physical examination protocol of the neck
[27], with amendments presented by Juul-Kristensen and co-workers
[26]. This protocol defines criteria for the diagnoses *Tension neck syndrome, cervicalgia, trapezius myalgia* and *cervical syndrome*.

#### Measurement of pressure pain threshold of neck muscles and pain provocation of neck facet joints

For quantification of muscle soreness in the upper trapezius muscles we use algometer pressure pain threshold (PPT) measurements. For acquaintance with the procedure, a first pressure pain test is performed distally of the left arm lateral epicondylia. Thereafter, the following measures are made: Right and left upper trapezius muscle, in the middle between processus spinosus of C7 and acromion, and a reference PPT in the tibialis anterior muscle of each leg. Three measurements are made on each spot, alternating between right and left side. The PPTs of the trapezius muscles are part of the decision model for treatment (see Table
2 and *Treatment components* above) as well as a secondary outcome measure (see below). Facets joints of the upper cervical spine are palpated for pain provocation and altered tissue resistance to movement as an indication of joint dysfunction
[59]. The facet joint assessment is only performed on participants who are suspected to have cervicogenic headache (see below).

#### Assessment of specific diagnoses

The assessment for cervicogenic headache is based on the major criteria of Cervicogenic Headache International Study Group
[54] with amendment of reduced ROM in the upper cervical segments and palpable upper cervical joint dysfunction
[55]. Examination of rhizopathy
[27] and vestibular dysfunction is made to comply with exclusion criteria. Participants who indicate pain in all four quadrants of the body in the pain drawing are examined for fibromyalgia/generalised pain
[40]. Participants are excluded if the diagnosis is confirmed.

### Questionnaires

The following questionnaires are used for treatment evaluation: *General improvement*, the Patient Global Impression of Change scale (PGICS)
[75]; *Pain intensity*, 0–10 Numeric Rating Scale (NRS)
[75]; *Pain localization*, pain drawing
[23]; *Physical functioning*, NDI
[24], *Symptoms and functional limitations*, the Profile Fitness Mapping neck questionnaire (ProFitMap-neck), a neck specific questionnaire
[28]; *Working capacity*, questions regarding the impact of neck symptoms on the quantity and quality of performed work
[25]. Self-estimated improvement during treatment is measured after 10 and 20 treatment sessions with PGICS and NRS.

For measurement of *health economy* EuroQoL 5-dimensions (EQ-5D)
[76] and the Short Form Health Survey (SF-36)
[77], reflecting health-related quality of life, are used. In addition, we apply measures of the cost of intervention, self-reported absence from work due to neck pain, prescription and consumption of drugs and health care, respectively.

Work load exposure is assessed by questionnaires and observations. *Psychosocial factors* are estimated by selected scales from the General Nordic Questionnaire for Psychological and Social Factors at Work (QPS Nordic)
[78]: Quantitative job demands; Decision demands; Learning demands; Control of decisions; Control of work pacing; Perception of mastery; Support from superior; Support from coworkers; Support from friends and relatives; Social climate. We also use a question on perceived stress with a 5-point response scale
[79]. Finally, *Physical factors* are assessed by observations in the workplace (Quick Exposure Check)
[80].

All participants allocated to the T- or NT-groups are also followed qualitatively during the intervention period through standardized as well as open ended questions after 10, 20 and at the last treatment session, respectively.

### Primary outcome measures

1. Physical functioning, measured with the Neck Disability Index (NDI)

2. Average pain intensity last week, measured with the Numeric Rating Scale (NRS)

### Secondary outcome measures

1. General improvement, assessed by the Patient Global Impression of Change scale (PGICS)

2. Symptoms, measured by the symptom index of the Profile Fitness Mapping neck questionnaire (ProFitMap-neck)

3. Capacity on the quality and quantity to work in the latest 6 weeks due to neck problems ([1 – (quality/10) × (quantity/10)] × 100%)

4. Pressure pain threshold of m. trapezius, assessed with pressure algometer measurement

### Other outcome measures

1. Self-estimated improvement during treatment, for General improvement, “much improved” or “very much improved” on PGICS; for Pain intensity, no pain last week (NRS)

2. Functional limitations and compound total score, assessed by the Profile Fitness Mapping neck questionnaire (ProFitMap-neck)

3. Cervical range of motion (active flexion-extension; active axial rotation; passive flexion-rotation)

4. Peak speed in cervical axial rotation

5. Cranio-cervical flexion endurance (50% of maximum voluntary contraction)

6. Lifting capacity, assessed by the cervical progressive isoinertial lifting evaluation test (C-PILE)

7. Physical activity, measured with LIV 2000

8. Health-related quality of life for clinical and economic appraisal, assessed by the EQ-5D

9. Questions on reporting sick, and consumption of care

10. Quality of life - Mental health, assessed by the Mental component summary in the SF-36

11. Quality of life – Physical Health, assessed by the Physical component summary in the SF-36

12. Area of pain distribution, assessed by pain drawings

13. Adverse events. Open ended questions, and PGICS administered after 10, 20 and the last treatment session. “Much worse” or “Very much worse” on the PGICS is equalized with an adverse event.

### Statistical methods

#### Power

Power calculations with the one-way analysis of variance (ANOVA) routine (nQuery Advisor 3.0) are presented with regard to treatment effects for the primary outcome measures Physical functioning, and Average pain intensity last week. For physical functioning measured with NDI, a clinical important difference is between 6–10 NDI%
[81]. Reference data from a parallel clinical trial (ISRCTN92199001) showed that the NDI standard deviation (SD) was 10.3 NDI% (based on 117 women with neck-shoulder pain). To obtain a power of 0.8, given a difference of 6 NDI% between any of the three groups, 20 individuals are required in each group (alfa = 0.05). For the average pain intensity last week, the smallest clinical important pain reduction measured with NRS is approximately 15%
[43]. In the above mentioned clinical trial, the SD was 15.5 NRS%. Given these facts, 20 individuals in each group is sufficient to obtain a power of >0.8 for a difference of 15 NRS% between any of the three groups (alfa = 0.05). On the basis of this power calculation we aim at recruiting 40 participants for each group, which would give us a satisfactory safety margin to retain a power of 0.8 or higher through the trial.

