## Methods/Design

### Design and setting

The study is a prospective interventional single-centre, single-assessor, blinded randomized controlled clinical trial. Participants with neck-shoulder pain will be allocated in a 1:1:1 ratio to either tailored (T) or non-tailored (NT) treatment two to three times a week for 11 weeks (in total 27 sessions) or to treatment-as-usual (TAU). Minimisation
[21,22] is used for the allocation sequence to minimise imbalance on the factors age, duration of pain, average pain intensity last week (Numeric Rating Scale – NRS) and disability due to neck pain (Neck Disability Index – NDI). Further, comparisons of baseline assessments will be performed with a control group without neck pain. The study will be executed in Umeå, Sweden. Assessment (questionnaires, laboratory and clinical assessments) of the participants with neck-shoulder pain is made one week before and after the treatment period, with follow-up measurements 6 and 12 month after end of treatment. The 12 month follow-up is only performed with questionnaires. See Figure
1 for a flow chart of the study. The study was approved by the Regional Ethical Review Board in Uppsala, Sweden (registration number 2011/081) and informed and written consent from participants is obtained according to the Declaration of Helsinki.

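### The NDI sample-size statement fails on its own inputs: 20 per group gives power of about 0.34 to 0.44 for 6 NDI%, and the planned 40 gives 0.63 to 0.76, not 0.8

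*Protocol article*

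**What the plan says.** The Power section of the protocol article (under Statistical methods) names its method: "Power calculations with the one-way analysis of variance (ANOVA) routine (nQuery Advisor 3.0"). For NDI it cites a clinically important difference of 6 to 10 NDI% and a parallel trial in 117 women, which "showed that the NDI standard deviation (SD) was 10.3 NDI"%. From these it states: "given a difference of 6 NDI% between any of the three groups, 20 individuals are required in each group", for power 0.8 at alpha 0.05. It makes a matching statement for pain intensity: 20 per group for a difference of 15 NRS% with SD 15.5.

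The recruitment target is then set at 40 per group, "which would give us a satisfactory safety margin to retain a power of 0.8 or higher through the trial". Allocation is 1:1:1 (Design and setting). The section gives no pattern for the three means, no baseline/follow-up correlation and no expected dropout. The Data analyses section plans ANCOVA with the baseline value as covariate, reporting between-group mean differences with 95% CIs.

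**The concern.** The same 20 per group is given for two quite different standardised effects: 6/10.3 = 0.58 for NDI and 15/15.5 = 0.97 for NRS. Required sample size goes roughly with the inverse square of the standardised effect, so NDI should need about (0.97/0.58)² ≈ 2.8 times as many participants as NRS.

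NDI is the first-listed primary outcome, and 6 NDI% is also the threshold the article uses to classify a participant as improved. If 20 per group were enough, the trial could lose half its participants and still be adequately powered for NDI. If it is not, heavy attrition may be tolerated wrongly, and a null tailored versus non-tailored result on NDI may be given more weight than it can bear.

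**Working it through.** **Inputs (protocol article, Power):** difference d = 6, SD = 10.3 (SD² = 106.09), three equal groups, alpha 0.05, target power 0.8, stated n = 20, planned n = 40.

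**Formulas.** For the one-way ANOVA, power comes from the noncentral F distribution with 2 and 3(n − 1) degrees of freedom and λ = n × Σ(μᵢ − μ̄)² / SD². For a pairwise contrast, it comes from the two-sided noncentral t distribution with 2n − 2 degrees of freedom and δ = (d/SD) × √(n/2).

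**Patterns of means.** The article does not fix the pattern, so three were tried:
- (0, 0, 6), one group differs: sum of squares 4 + 4 + 16 = 24. This is the most favourable pattern when the largest difference is 6.
- (0, 3, 6), evenly spaced: 9 + 0 + 9 = 18. This is the least favourable such pattern.
- (0, 6, 12), neighbouring groups 6 apart: 36 + 0 + 36 = 72. The outer groups then differ by 12.

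**Attempt to reproduce n = 20:**
- (0, 0, 6): λ = 20 × 24/106.09 = 4.52; power 0.44
- (0, 3, 6): λ = 20 × 18/106.09 = 3.39; power 0.34
- (0, 6, 12): λ = 20 × 72/106.09 = 13.57; power 0.905
- Pairwise t: δ = 0.5825 × √10 = 1.84; power 0.435

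None gives 0.8 at 20.

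**Power and required n:**

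| Reading | n = 20 | n = 40 | n for 0.8 |
|---|---|---|---|
| (0, 0, 6) | 0.44 | 0.76 | 44 |
| (0, 3, 6) | 0.34 | 0.63 | 58 |
| Pairwise t, two-sided | 0.43 | 0.73 | 48 |
| Pairwise t, one-sided (not stated in the article) | 0.565 | 0.83 | 38 |
| (0, 6, 12) | 0.905 | 0.998 | 16 |

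With an assumed 15% loss (40 × 0.85 = 34 per group), the first three rows give 0.69, 0.55 and 0.66.

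**Difference detectable with power 0.8:**
- At n = 20: 9.0 (one group differs), 10.4 (even spacing), 9.4 (pairwise)
- Pairwise at n = 40: 6.5
- Pairwise at n = 34: 7.1

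So 20 per group corresponds to roughly the top of the quoted 6 to 10 range, not to 6.

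**Check of the method on the NRS statement** (d = 15, SD 15.5, n = 20): 0.88 for (0, 0, 15) and 0.85 pairwise, so the article's claim of more than 0.8 is recovered. Evenly spaced means (0, 7.5, 15) give 0.765. Under the two readings that support the NRS claim, NDI power is only 0.44 and 0.43.

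**Gain from ANCOVA.** If 10.3 is the unadjusted SD, the adjusted SD is 10.3 × √(1 − r²), where r is the baseline/follow-up correlation. The article gives no r. The r needed for power 0.8 is:

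| n per group | (0, 0, 6) | Pairwise t | (0, 3, 6) |
|---|---|---|---|
| 20 | 0.75 | 0.77 | 0.82 |
| 40 | 0.30 | 0.40 | 0.56 |

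At 34 per group the pairwise contrast needs r of about 0.54. With an assumed r = 0.5, the adjusted SD is 10.3 × 0.866 = 8.92 and pairwise power is 0.84 at n = 40 and 0.78 at n = 34.

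**The case against.** The strongest defence concerns the planned 40 rather than the stated 20. The primary analysis is a baseline-adjusted ANCOVA, and a moderate correlation would bring 40 per group to 0.8 for a pairwise contrast. This stands in part: the shortfall at 40 is established only for the unadjusted one-way ANOVA and t-test inputs that the article prints, and power under the planned analysis is undetermined. It does not vindicate the margin claim, which rests on an unadjusted calculation with no correlation. Even at r = 0.5, an assumed 15% loss takes pairwise power to 0.78.

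A second defence reads the difference as 6 between neighbouring groups, (0, 6, 12), which fits an ordering of tailored, non-tailored and usual treatment. Twenty per group would then suffice, with power 0.905. But the requirement would be 16, not 20, and tailored and usual treatment would differ by 12 NDI%, outside the quoted 6 to 10 range. What stands is that the pattern of means is unstated. Every pattern with a largest difference of 6 fails.

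One-sided testing does not help the stated figure: it still needs 38 per group, and nothing in the article says the tests are one-sided.

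Finally, the planned 95% CIs would show imprecision, which reduces the risk of misreading a null result. That is fair, but it does not make the printed sample size correct.

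**Conclusion.** The concern holds. For a largest between-group difference of 6 NDI% with SD 10.3 at alpha 0.05, 20 per group gives power 0.34 to 0.44 rather than 0.8. The true requirement is 44 to 58 per group, more than twice the stated number even in the best case. On the same unadjusted inputs, the planned 40 gives 0.63 to 0.76 before attrition, so the safety-margin claim also fails for NDI.

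The error at 20 does not depend on the choice between the F test and a two-sided or one-sided t test. It would disappear only with an unstated correlation of about 0.75 to 0.82, or if the outer groups differed by 12. The shortfall at 40 is conditional on no baseline adjustment. The NRS statement is broadly sound, except under evenly spaced means (0.765).

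**What to change.** Rewrite the NDI part of the Power paragraph; do not change enrolment.

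- State that 6 NDI% with SD 10.3 needs about 48 per group for a two-sided pairwise comparison, or 44 for the ANOVA when one group differs, and name the pattern of means assumed.
- State that 40 per group gives about 0.73 pairwise (0.76 for that ANOVA) before attrition, and reaches 0.8 pairwise for about 6.5 NDI%.
- Remove the safety-margin claim for NDI as it stands. If the ANCOVA gain is to be relied on, state the assumed correlation, its source and the resulting power with and without loss to follow-up (for example r = 0.5: 0.84 at 40 and 0.78 at 34 per group). Restore a margin claim only if those figures support it.
- Base the calculation on the pairwise contrasts that the hypotheses concern, rather than on the overall F test.

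The cost is one reworded paragraph and a less favourable power statement for a primary outcome. No participants are added and the design is unchanged.
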